### Data collection

#### Work package 1

Quantitative data collected in the point prevalence study will be obtained using freedom of information act requests. Returned data will be cleaned and standardised ahead of analysis. The information request will be piloted on 5% of sites initially and any changes made as required.

#### Work package 2

Interviews will be semi-structured to allow flexibility whilst maintaining structure to cover key concepts. The interview guide will be developed by the researcher and reviewed by academics, stakeholders and patients and members of the public. This includes the research team consisting of nurses and dietitians and wider professional stakeholder group (including paediatricians and speech and language therapists) who will meet online to discuss the guide. PPIE input will be provided by a group of parent carers involved in the study throughout who will be involved to pilot the interview guide. Interview questions will be informed by the theoretical domains framework to elicit understanding of behavioural influences (Atkins et al., 2017). Interviews will be carried out remotely using videoconferencing software or by phone as per participant preference. Face-to-face interviews may be accommodated if preferred. Interviews will be recorded and transcribed verbatim ahead of data analysis. Single interviews have been chosen to minimise burden on participants who are likely to have significant health needs or caring responsibilities. Interviews will be scheduled at times to suit the participant.

#### Work package 3

The Delphi study will consist of up to three rounds. The first will be based on findings from the interview study including themes generated from the analysis. These will highlight identified barriers and strategies to address them which participants will assess and determine their importance. Free text boxes will allow participants to suggest ways that these barriers may be addressed. Rounds two and three will gain consensus on barriers and prioritise ways that they can be addressed which will inform the development of an intervention. A cut off between 70% and –80% will be used and agreed with the team with input from stakeholders and patients and members of the public. Given that this research is exploratory and comprises early stages of complex intervention development, a lower level of agreement may be acceptable.

### Data analysis

The point prevalence of blended diet use will be calculated for each organisation and descriptive statistics (e.g. mean, median) will be calculated for the whole data set as well as separately for children (0–17 years) and young people (18–25 years).

Reflexive thematic analysis will be used for the interview study (Braun and Clarke, 2019). This supports a realist approach to offering an explanatory understanding of the context and mechanisms affecting the use of blended diets recognising the co-creation of knowledge between the researcher and the data. A proportion of the interview recordings will be transcribed by the researcher to aid familiarisation; any transcribed externally will be read multiple times. Interview transcripts will be coded by the researcher by identifying meaningful words and phrases. Codes will then be grouped into themes and labelled to summarise important topics in the data collected.

Coded data will also be used to refine the programme theory. Data will provide evidence to confirm, refine or refute the programme theory through an iterative process involving stakeholders and patients and members of the public. Causal mechanisms and their influence on outcomes of interest will be explained using CMOCs.

Data analysis in the Delphi study will involve calculating frequencies of responses, medians and interquartile range of Likert scales. Qualitative data from free text responses will be analysed using reflexive thematic analysis as with the interview data. Response rates, drop-outs and characteristics of the panel will be monitored and reported in the study findings. Data from the Delphi study will be used to further refine the programme theory through iterations of the CMOCs.

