## Aim

To explore factors affecting the use of blended diets for children and young people in health, education and social care settings in the UK.

Objectives:
Identify the prevalence of the use of blended diets for children and young people across the UK.Explore views and experiences of health, education and social care professionals and families to determine the context and underlying mechanisms affecting the use of blended diets.Identify and prioritise components of an intervention to support the delivery of blended diets in health, education and social care settings.

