**Figure 2. fig2-02601060261439096:**
[figure not shown]
Mixed methods study design.

Integration is key to mixed methods studies whereby both methods ‘are in dialogue’ (Plano Clark, 2019) with each other. In this study, findings from the point prevalence study (work package 1) will inform the sampling of participants for the interview study (work package 2). Participants for the interview study (work package 2) will be recruited through NHS organisations with high prevalence of blended diet use. This will support rich data collection about the contexts and mechanisms supporting their use. Initial rounds of the Delphi study (work package 3) will be informed by the interview data so that contextual factors and influential mechanisms identified can be ranked and prioritised ahead of subsequent stages of intervention development.

Mixed methods studies are suited to understanding complex phenomena which cannot be adequately explored using qualitative or quantitative methods alone (Plano Clark, 2017). Mixed methods research supports an understanding of ‘how’ and ‘why’ rather than simply ‘what’ which is key in this research which is complex and nuanced. The aim of using mixed methods in this study is to establish generative causation, necessary for realist research; quantitative methods can identify patterns whilst qualitative insights identify the causal mechanisms.

A Good Reporting of a Mixed Methods Study (GRAMMS) checklist can be seen in Appendix 1 (O'Cathain et al., 2008).

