### Sampling and recruitment

All NHS organisations will be considered for inclusion in the point prevalence study which will identify the number of people using home enteral tube feeding and of those, the proportion using a blended diet. They will be contacted using freedom of information act requests to obtain data on prevalence of home enteral tube feeding and use of blended diets.

Purposive sampling for the interview and Delphi study will ensure that participants have the relevant knowledge, experience and expertise of blended diets necessary to gather rich, in-depth data (Palinkas et al., 2015). Participants will be recruited through NHS trusts and health boards and other organisations such as special needs schools and hospices to achieve a diverse sample. Eligibility criteria for the interview and Delphi study are the same, and participants can partake in one or both. Additional participants may also be recruited using a snowballing method. Authors acknowledge that participants included in the study may have experienced different or fewer barriers to families without awareness or experience of blended diets. However, an understanding of ways that barriers have been overcome was deemed an insightful first step in developing knowledge on the topic.

A sampling framework will be used to capture those with a range of experience (length of time using a blended diet or professional background). The framework provides an approximate sample size and may be adjusted according to the conceptual depth of the data collected (see Appendix 2). Multi-disciplinary Delphi panels need to be larger to capture a range of participants as is the case with this study (Manyara et al., 2024). In addition, PPIE representatives have explained that due to the fluctuating care needs of their children, their availability to partake may vary. For this reason, a larger panel may be necessary to accommodate a higher than usual drop-out rate. It is generally advised to seek a minimum panel size and ensure representation of subgroups (Beiderbeck et al., 2021; Page et al., 2015).

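### The analysis names only summaries of organisation-level prevalences, while objective 1 asks for the share of UK tube-fed children and young people using a blended diet

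*Protocol article*

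**What the plan says.** All references are to the protocol article.

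- **Aim, objective 1:** "Identify the prevalence of the use of blended diets for children and young people across the UK".
- **Sampling and recruitment:** the point prevalence study is to "identify the number of people using home enteral tube feeding and of those, the proportion using a blended diet". This is a person-level definition. The denominator is people on home enteral tube feeding and the numerator is those of them on a blended diet. The frame is wide: "All NHS organisations will be considered for inclusion in the point prevalence study".
- **Data analysis:** the unit becomes the organisation. Point prevalence will be "calculated for each organisation and descriptive statistics (e.g. mean, median) will be calculated for the whole data set", with the same for ages 0–17 and 18–25.
- **Study design:** the organisation-level figures have a second use. "Participants for the interview study (work package 2) will be recruited through NHS organisations with high prevalence of blended diet use".

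The article does not name a total over all organisations, or a mean weighted by caseload, as the UK figure.

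**The concern.** The objective and the analysis use different units. The objective concerns people. The named summaries concern organisations, because with one proportion per organisation a mean or median is naturally taken across those proportions. Unless it is weighted, such a mean counts a service with a handful of tube-fed patients as much as a large regional service. It answers what prevalence looks like in a typical organisation, and not what share of tube-fed children and young people in the UK use a blended diet.

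The article itself gives reason to expect differences between organisations. Its Background says that some organisations prohibit blended diets and, on anecdotal evidence, that support varies across the UK. If prevalence also differs between large and small services, the two questions have different answers.

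At stake is the national figure that the study would report as the scale of blended diet use, overall and in each age band. No test, sample size or clinical decision depends on it.

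**Working it through.** The plan states no prevalence, caseload or sample size for work package 1, so there is no figure of its own to reproduce. The check compares the two kinds of summary algebraically and then on assumed data.

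**Notation.** Organisation i has n_i people on home enteral tube feeding, x_i of them on a blended diet, and prevalence p_i = x_i / n_i. There are k organisations.

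**Formulas.**
- Person-level (pooled) prevalence: P = Σx_i / Σn_i. Since x_i = n_i p_i, this is the mean of the p_i weighted by n_i.
- Mean over organisations, each counted once: M = Σp_i / k.
- Difference: P − M = cov(n, p) / mean(n). The mean equals the pooled value only when prevalence and caseload are uncorrelated.
- The median of the p_i has no such identity.

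**Assumed caseloads (not in the document):** 100 organisations with 20 patients and 20 with 300. Total 100×20 + 20×300 = 8,000 patients in 120 organisations.

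| Small / large prevalence | Pooled | Mean | Median |
|---|---|---|---|
| 10% / 10% | 800/8,000 = 10.0% | 10.0% | 10% |
| 10% / 12% | (200+720)/8,000 = 11.5% | (100×10+20×12)/120 = 10.3% | 10% |
| 10% / 15% | (200+900)/8,000 = 13.75% | (100×10+20×15)/120 = 10.8% | 10% |
| 5% / 20% | (100+1,200)/8,000 = 16.25% | (100×5+20×20)/120 = 7.5% | 5% |
| 20% / 5% | (400+300)/8,000 = 8.75% | (100×20+20×5)/120 = 17.5% | 20% |

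Check of the identity on the 5% / 20% row: mean(n) = 8,000/120 = 66.67. The mean of n×p is 1,300/120 = 10.83. The covariance is 10.83 − 66.67×0.075 = 5.83, and 5.83/66.67 = 8.75 points. Adding this to 7.5% gives 16.25%.

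**Size of the gap for the mean.** It is 11.5 − 10.3 = 1.2 points in the mildest unequal case. In the two strongest cases the ratio is 16.25/7.5 = 2.2 and 17.5/8.75 = 2.0. The strong cases need a fourfold difference in prevalence between small and large services.

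**The median with equal caseloads.** Take 10 organisations of 100 patients, 4 at 20% and 6 at 5%. Pooled: (80+30)/1,000 = 11.0%. Mean: 11.0%. Median: 5.0%. Equal caseloads repair the mean but not the median.

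**The case against.** **The list is open.** The summaries are introduced by "e.g.", and the phrase about the whole data set does not say what is averaged. A pooled proportion is compatible with the text and with the person-level definition under Sampling and recruitment. This stands in part. A reader might infer that the plan prescribes an unweighted mean as the UK estimate, but the article never says "unweighted" and never labels the mean or median as the UK figure. What remains is that the only summaries named, on their natural reading, do not estimate objective 1. A median over organisations is not a pooled proportion under any reading.

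**This is a condensed article.** A reader might also count as defects the lack of a stated confidence interval and of a rule for organisations with no eligible patients. An article commonly leaves both to the fuller document, so neither is a finding. The choice of unit and summaries is different, because the article does state it.

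**The error may be small.** This stands. A reader might take the strongest rows of the table to mean that the headline will be wrong by a factor of two whenever prevalence is related to caseload. The milder rows show otherwise.

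**Choice of interview sites.** A reader might infer that ranking organisations by raw prevalence selects mostly chance-high small services. That follows only if true prevalence is much the same everywhere, which sits badly with the Background. In a simulation of 150 organisations (assumed lognormal caseloads, median 40, log-SD 1.0), a between-organisation SD of 1 on the logit scale gave a top 15 with mean true prevalence 47% against 53% observed. With an SD of 0.5 the figures were 26% and 36%. Some inflation and drift to smaller services remain (median caseload in the top 15 about 36 and 28), but selection still finds services with high use. The sampling is purposive and seeks rich data, so organisation-level prevalence is the right unit for that step.

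**Conclusion.** The point holds as a mismatch between objective and named analysis. Objective 1 is a proportion of people. The Data analysis section calculates prevalence per organisation and names only a mean and median, with no pooled or caseload-weighted figure. Followed as written on the natural reading, it describes the typical organisation.

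The size of the resulting error cannot be found from the document, because it depends on how prevalence varies with caseload. Under the assumed caseloads the mean ranges from equal to the pooled value (no relation), through about one percentage point off (weak relation), to a factor of about two in either direction (fourfold difference in prevalence). The median can be further off. The same reasoning applies within each age band.

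This is worth settling before the work package 1 data are analysed. It is not irreversible: if the numbers described under Sampling and recruitment are returned, the pooled figure can be calculated at any time. Organisation-level prevalences are not wrong in themselves. They suit the description of variation and the choice of interview sites.

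**What to change.** In the Data analysis section:

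1. State that the headline estimate for work package 1 is the total number of blended diet users divided by the total number of eligible home enteral tube feeding users across responding organisations, for ages 0–25, 0–17 and 18–25.
2. Preferably add a 95% confidence interval that allows for clustering by organisation.
3. Keep the mean, median and spread of organisation-level prevalences, labelled as a secondary description of variation between organisations.

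For work package 2, organisation-level prevalence can stay as the basis for choosing sites. A minimum denominator there is optional.

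The cost is a few sentences. The numbers needed are those the information request already seeks, provided they are returned for each age band, which the planned age-specific summaries require in any case.

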### Reflexivity

Researcher reflexivity is integral due to the qualitative nature of the study. Reflexive journaling and team discussions will capture how researcher beliefs and experiences influence the study (Olmos-Vega et al., 2023). These influences will be reported with the findings of the study to highlight the impact on decision making throughout the study.

### Equality impact assessment

Equality impact assessments are becoming increasingly embedded in health and social care research to understand how research practices affect people differently and ways that they can be accommodated (NIHR, 2025). Minority groups have historically been excluded from research and it is necessary that they are included to ensure that clinical practice is underpinned by inclusive research to be truly evidence-based (Brooker et al., 2014). Given the focus of enteral tube feeding, it was deemed likely to positively impact people with disabilities by advancing knowledge on a topic relevant to this under-served group. The assessment involved consideration of all protected characteristics to optimise inclusion in the study. Some methodological considerations resulting from the equality impact assessment can be seen in Box 1.

Box 1.Methodological considerations resulting from equality impact assessmentAge:
The age range of children and young people is inclusive of young people up to 25 years.The readability of participant information materials has been assessed to ensure that they are suitable for the target population.Disability:
Remote data collection methods, for example, online or phone interviews were deemed more suitable for this group by patients and members of the public.Race or religion:
Recruitment methods include sampling through the NHS to increase opportunity for participants to be involved.Timing of data collection will aim to avoid religious festivals such as Ramadan.Flexibility when planning interviews will accommodate people from different groups such as those who work or have caring responsibilities.The research has been designed with input from a diverse PPIE group.

### Patient and public involvement and engagement

Inclusion of PPIE in healthcare research adds invaluable insight which can optimise the quality, relevance and application of the research (Arumugam et al., 2023). Figure 3 shows some examples of how PPIE has been and will be embedded in this study.

**Figure 3. fig3-02601060261439096:**
[figure not shown]
Patient and public involvement and engagement (PPIE) input.

Early PPIE identified the need for research on this topic. Formal PPIE activity informed the study design and grant application for this research and identified that subsequent PPIE must accommodate those with significant caring responsibilities of children and young people with fluctuating health. As a result, a flexible approach using remote ways of working has been incorporated in this study.

The group consists of parent carers of tube-fed children and young people, both male and female from a range of ethnic backgrounds. Group members were invited through a national tube feeding charity (PINNT), social media and clinicians involved in the study. Group members are invited to meetings or asked for input, with the option to participate as their availability allows, without pressure to commit. Online meetings have proven effective; those unable to attend can stay informed through meeting minutes or recordings. PPIE input has shaped recruitment materials, imagery and the wording of participant information sheets. Their involvement in reviewing aspects such as survey length has helped ensure that participation is not burdensome, thereby enhancing accessibility.

## Ethics and dissemination

Ethical approval for this study has been granted by NHS Health Research Authority South Birmingham Research Ethics Committee (REC reference: 25/WM/0099).

All participants will provide informed consent and may withdraw at any time without giving a reason. Participant information sheets (PIS) have been assessed for readability and written in plain English. All data will be stored securely, and interview transcripts will be pseudonymised on transcription.

Young people (16–25 years) are eligible to take part and a separate PIS will be developed including an easy read version for inclusivity. Young people can choose to bring someone with them if they choose. The researcher will complete interviews in a private room to maintain confidentiality of participants. The interview topic is not inherently distressing; however, interview will be paused if the participant becomes distressed. In this instance, participants will be offered the choice to continue, postpone or terminate the interview.

Participants will be asked to provide an email address if they wish to be updated with the study findings. The research team will write participant summaries in plain English and ask PPIE representatives to review them and advise of other networks to share the study findings. On completion, the study will be submitted for publication in international peer-reviewed journals, presented at topic specific conferences and shared within professional networks. A policy briefing will also support the translation of the findings into practice.

## Summary

This paper describes the protocol for a novel, mixed methods study exploring contexts and mechanisms affecting the use of blended diets for children and young people in health, education and social care settings in the UK. Inspired by families with lived experience of using blended diets, it will progress knowledge of this topic area further expanding the evidence base underpinning practice in this area which is currently lacking. This study will underpin subsequent development of a complex intervention to support the use of blended diets in health, education and social care settings by identifying influential contexts and mechanisms. This understanding will enable subsequent interventions, focusing on the implementation of blended diets, to be appropriately targeted optimising efficiency and effectiveness. The significance of this study relates to the specific requirement identified by families using blended diet. This is the need for research to support the use of blended diets which this study aims to address. Families explained that challenges remain with using blended diets away from home and a lack of consistent support across settings accessed by tube-fed children and young people.

The strengths of this study lie in the use of mixed methods to gain a comprehensive answer to the research question. Data integration is cohesive across the work packages for a truly mixed methods approach. The study is both data-driven and theoretically informed, ensuring that findings will be systematically interpreted and grounded within relevant conceptual frameworks. A realist lens ensures that the phenomena are studied within context enhancing external validity and therefore applicability to policy and practice. A nationwide approach will increase the transferability of findings and inform a standardised approach to development in this area of practice for those accessing NHS services.

Findings from this study will inform future research on interventions to better support blended diets to optimise choice. It provides a rigorous foundation for future developments in this area centred around the needs of children, young people and their families.

